### Sample size calculation

Prior research conducted by the authors indicates that attrition rates for CBT trials with this sample are, on average, 18% over a 12-month study period following treatment. Thus at 24-month follow-up in the current study (approximately 12 months following the end of treatment), 205 participants will likely remain in the study (102 per treatment condition). Regular contact at every 6 month interval until 36 months post baseline is likely to retain this sample size. This will provide sufficient statistical power (80%) to detect moderate population differences of the order of 0.5 of a standard deviation, using conventional 0.01 level, 2-tailed tests for the primary variables of interest. This is the equivalent of a differential change of approximately 7 cigarettes per day or 13 points on the 100 point CVD risk score, both moderate but clinically useful differences.

### Statistical Analysis

Data coding and analysis will be carried out by the authors using available software packages (e.g. Statistical Package for Social Sciences for Windows). Variables hypothesised to change over time according to treatment allocation will be examined predominantly using generalized linear mixed models, techniques that facilitate management of missing data without imputing values or excluding participants. Chi-square analyses or binary logistic regressions will be performed on categorical outcome variables. Primary outcome measures will typically be analysed in two ways: (1) intention to treat (with study dropouts regarded as continuing smokers and/or with unchanged CVD risk relative to baseline); and (2) analyses performed within the sub-sample of participants who completed the majority of treatment sessions. In addition, comparisons on selected demographic and clinical characteristics will be made between this sub-sample and those who dropped out of treatment, to help detect any biases in outcome measures. Other potential confounders will also be examined (e.g. involvement in additional treatments) and their potential effects modelled in the major analyses (e.g., controlling and not controlling for these variables). As a partial control for the number of statistical tests, the threshold for significance will be set at p < 0.01.

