### Study design & setting

This is a prospective randomised controlled comparison study. Figure 1 shows the overall design. After completion of a baseline assessment and an initial face-to-face intervention session, participants will be randomly assigned to either a multi-component intervention for smoking cessation and CVD risk reduction or a telephone-based minimal intervention focusing on smoking cessation. Randomisation will be stratified by site (Newcastle, Sydney, Melbourne, Australia), Body Mass Index (BMI) category (normal, overweight: ≥ 25 and < 30; obese: ≥ 30) and type of antipsychotic medication (typical, atypical). A permuted block randomisation approach will be used so that the distribution of participants across treatment conditions will be maintained regardless of the final sample size. Following completion of the baseline assessment for each participant, the clinicians will be issued with a sealed randomisation envelope (by an independent person) which displays the participant identification code. The envelope will be opened by the participant at the conclusion of the initial session. This research will be conducted in three sites: Centre for Brain and Mental Health Research, University of Newcastle, New South Wales (NSW); School of Public Health, University of NSW, Sydney, NSW; and the Monash Alfred Psychiatry Research Centre (MAPrc), Monash University and The Alfred, Melbourne, Victoria, Australia. The researchers involved are experienced clinicians and scientists. Ethical approval was obtained for this study through the lead site of Hunter New England Human Ethics Committee and at each site.

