### Inclusion Criteria

1) Age 18 years and over (minimum age level recommended for the use of nicotine replacement therapy, NRT);

2) Diagnosis of a severe mental disorder, as confirmed by the Mini International Neuropsychiatric Interview (MINI; [7]) - schizophrenia spectrum or bipolar disorder;

3) Current smoker (at least 15 cigarettes per day); and

4) Taking antipsychotic medication as prescribed for a period of at least two months, with intention to continue for the duration of the study.

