As in the pilot study, the two primary outcome variables will be: (i) overall CVD risk index for participants; and (ii) smoking status; while the secondary dependent variables will include: weight; physical activity; unhealthy eating; substance use; psychiatric symptomatology; treatment retention and treatment alliance; service utilisation; general functioning; and quality of life. The CVD risk index calculation will be performed using the National Vascular Disease Prevention Alliance Absolute Risk Assessment [11] which is based on the Framingham algorithms [12]. Within this index, multiple risk factors of age, gender, systolic blood pressure, cigarette smoking, cholesterol and diabetes are used to predict CVD risk over 5 years [11]. Blood pressure measurements will be taken, as well as a small blood sample by finger prick to measure cholesterol and blood glucose levels. A general health and well-being questionnaire will also be completed by participants to identify lifestyle habits and previous medical history. Smoking status will be determined according to point prevalence abstinence (last 7 days) and continuous abstinence (since quit attempt), both of which will be biochemically validated by a CO reading of ≤10 ppm. Additionally, we will use 50% reduction in cigarettes per day as an indicator of smoking status [13].

We also plan to report the cost of delivering the intervention in real world settings and the cost impacts of the outcomes achieved by calibration of selected instruments used in the study (e.g. Quality of Life Scale, Global Assessment of Functioning) with those achieved in other costing studies.

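### The plan lets the primary smoking outcome be tested by an unadjusted chi-square although allocation is stratified by three factors; the likely loss is small and the remedy nearly free

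*Protocol article*

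**What the plan says.** In the protocol article, Study design & setting states "Randomisation will be stratified by site (Newcastle, Sydney, Melbourne, Australia), Body Mass Index (BMI) category" and goes on to add type of antipsychotic. That gives 3 sites x 3 BMI categories x 2 medication types = 18 strata. Allocation within them is blocked: "A permuted block randomisation approach will be used so that the distribution of participants across treatment conditions will be maintained".

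Outcome Measures makes smoking status one of two primary outcomes: "Smoking status will be determined according to point prevalence abstinence (last 7 days) and continuous abstinence (since quit attempt". It adds "we will use 50% reduction in cigarettes per day as an indicator of smoking status". Each of these indicators is binary.

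Statistical Analysis has two sentences on method. The first is "Variables hypothesised to change over time according to treatment allocation will be examined predominantly using generalized linear mixed models"; the second is "Chi-square analyses or binary logistic regressions will be performed on categorical outcome variables". On adjustment, the section says that other potential confounders will be examined and "their potential effects modelled in the major analyses (e.g., controlling and not controlling for these variables". The one example it gives is use of additional treatments. Site, BMI category and antipsychotic type do not appear in the section.

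**The concern.** When allocation is stratified on a factor that predicts outcome, the arms are balanced on it by design. An analysis that leaves the factor out still puts the variation it explains into the error term. The test is then somewhat conservative, and precision that the design has secured is not used. A chi-square test has no place for these factors or for a baseline measure of smoking intensity.

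Two features make this more than a missing covariate list. The text expressly permits the unadjusted test on a primary outcome. The only adjustment variable it names, additional treatment, is recorded at each assessment (Exclusion Criteria), so at follow-up it can be affected by arm. The three factors fixed before randomisation go unmentioned. At stake is some power for abstinence in a trial that tests at 0.01.

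**Working it through.** **The plan's own figure.** Sample size calculation gives 102 per arm, 0.5 SD, two-sided alpha 0.01 and 80% power.
- Retention: 250 x 0.82 = 205, as stated.
- Power = Φ(0.5/√(2/102) − 2.576) = Φ(3.571 − 2.576) = 84.0%; with the noncentral t, 83.3%.
- The difference detectable at 80% power is 0.479 SD (t: 0.483).

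The stated 80% is therefore rounded on the safe side. It concerns a continuous outcome; the section gives no abstinence rates, so there is no planned power for abstinence to reproduce.

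**Cost of an unadjusted chi-square for a binary smoking outcome.**

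Inputs from the protocol: 250 participants, all kept because the intention-to-treat analysis counts dropouts as smokers; 18 strata; permuted blocks; two-sided alpha 0.01.

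Inputs assumed, because the protocol does not give them:
- block size 4;
- site shares 40/30/30%, BMI shares 25/35/40%, typical/atypical 15/85%, in that order of coding;
- control logit −2.0, i.e. 1/(1 + e^2.0) = 11.9% where the factors have no effect;
- treatment log-odds ratio 1.1 (odds ratio 3.0), giving 1/(1 + e^0.9) = 28.9% in the intervention arm;
- factor effect on the logit = b x (site score −1, 0, 1; plus half a BMI score −1, 0, 1; plus half a medication score −1, 0), with b = 0, 0.4 or 0.8.

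Each scenario used 4,000 simulated trials. The chi-square was compared with a logistic likelihood-ratio test containing main effects for the three factors.

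| Strength of the factors | Chi-square power | Adjusted power | Gain (points) | Chi-square type I | Adjusted type I |
|---|---|---|---|---|---|
| none (b = 0) | 79.4% | 80.4% | 0.9 | 0.88% | 1.18% |
| moderate (b = 0.4) | 77.8% | 80.0% | 2.1 | 0.78% | 0.90% |
| strong (b = 0.8) | 73.7% | 78.0% | 4.3 | 0.88% | 1.30% |

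Gains are taken before rounding. Monte Carlo standard errors are √(0.01 x 0.99/4000) = 0.16 points for type I error and about √(0.8 x 0.2/4000) = 0.6 points for each power.

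**Reading the table.** The gain grows with the strength of the factors, as theory predicts. The 0.9 points at b = 0 cannot come from the factors, which there predict nothing; they reflect the likelihood-ratio test rejecting slightly more often under the null. The chi-square type I errors lie below 1% by less than 1.5 standard errors each. The simulation thus agrees with mild conservatism but does not measure it precisely.

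**What a baseline value can add for smoking.** Entry requires "Current smoker (at least 15 cigarettes per day", so baseline abstinence is constant and adjusting for it gains nothing. Baseline cigarettes per day and the Fagerstrom score can vary above that floor, and Table 1 collects the smoking measures at baseline. Their gain is not quantified here.

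**The case against.** The strongest reply is that the sentence offers logistic regression as an alternative, and that can carry every factor. The preceding sentence sends outcomes that change over time mainly to mixed models, a class that includes logistic ones. The section also foresees covariate modelling, with additional treatments only as an example. The article condenses a fuller plan, and covariate lists commonly sit there. All of this stands: a reader might infer that the plan commits to an unadjusted chi-square at each visit, and the text does not say so. What survives is narrower. The choice is left open for a primary outcome, and one of the stated options is the weaker one.

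A reader might also infer a large loss of power from the usual baseline-adjustment formula. With 102 per arm and 0.5 SD, multiplying the SD by √(1 − r²) raises power from 84.0% to 93.9% at r = 0.5 and 99.2% at r = 0.7. Those figures do not measure this problem. They concern a continuous outcome such as the CVD index, which the chi-square sentence does not govern. The correlations are assumed. The starting point is a follow-up-only t-test that the plan does not specify, and a mixed model that includes the baseline occasion may already use the correlation.

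**Conclusion.** The point holds as a minor, nearly free improvement. The plan permits an unadjusted chi-square on the primary smoking outcome and does not carry the stratification factors into the analysis. If that option is taken, the test is slightly conservative (type I error about 0.8-0.9% against 1%) and gives up about 1 to 4 points of power, part of which is the adjusted test's higher type I error. These sizes rest on the assumed event rates, stratum shares, block size and prognostic strengths listed above.

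A reader might conclude that ignoring the strata invalidates the test. It does not: the error is on the safe side, and the cost is precision only.

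**What to change.** In Statistical Analysis, or in the SAP if it is still open:

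1. For the primary smoking outcome, remove the chi-square option. Specify a logistic model, ordinary or mixed, with arm, main effects for site, BMI category and antipsychotic type (5 degrees of freedom, not the 18 cells), and baseline cigarettes per day or Fagerstrom score. Choose one of the two in advance.
2. In the mixed model for the CVD risk index, include the same three factors and state that the baseline index is used, either as a covariate or as a baseline occasion.
3. Because a covariate-adjusted odds ratio differs from the crude one, report a marginal risk difference for abstinence beside it.

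The cost is wording only. The stratification factors are known at randomisation and the smoking and CVD measures are already taken at baseline, so no data, visits or participants are added.

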**Methods/Design:**

250 smokers with a severe mental disorder will be recruited. After completion of a baseline assessment and an initial face-to-face intervention session, participants will be randomly assigned to either a multi-component intervention for smoking cessation and CVD risk reduction or a telephone-based minimal intervention focusing on smoking cessation. Randomisation will be stratified by site (Newcastle, Sydney, Melbourne, Australia), Body Mass Index (BMI) category (normal, overweight, obese) and type of antipsychotic medication (typical, atypical). Participants will receive 8 weekly, 3 fortnightly and 6 monthly sessions delivered face to face (typically 1 hour) or by telephone (typically 10 minutes). Assessments will be conducted by research staff blind to treatment allocation at baseline, 15 weeks, and 12-, 18-, 24-, 30- and 36-months.

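### The ITT rule carries baseline CVD risk forward for dropouts although the mixed models are chosen to avoid imputation; the governing rule is unstated, and under missing at random the frozen version shrinks the effect

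*Protocol article*

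**What the plan says.** Outcome Measures states that "the two primary outcome variables will be: (i) overall CVD risk index for participants; and (ii) smoking status". The CVD index is an absolute risk score in which "multiple risk factors of age, gender, systolic blood pressure, cigarette smoking, cholesterol and diabetes are used to predict CVD risk over 5 years".

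Statistical Analysis then makes three statements that all bear on CVD risk:

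- "Variables hypothesised to change over time according to treatment allocation will be examined predominantly using generalized linear mixed models", described as "techniques that facilitate management of missing data without imputing values or excluding participants".
- The primary outcomes will typically be analysed in two ways, the first being "intention to treat (with study dropouts regarded as continuing smokers and/or with unchanged CVD risk relative to baseline".
- The second way is "analyses performed within the sub-sample of participants who completed the majority of treatment sessions".

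Sample size calculation states that "attrition rates for CBT trials with this sample are, on average, 18% over a 12-month study period following treatment". It therefore bases power on 205 retained participants, 102 per arm, out of 250.

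**The concern.** Giving a dropout the baseline value of the index is an imputation, and restricting to those who attended most sessions is an exclusion. The mixed models were chosen to avoid both. Neither of the two analyses named for the primary outcomes is described as a mixed model on everyone's observed data, and nothing in the article ranks the three approaches. The sample size adds to the uncertainty: it counts 205 people with data, whereas the ITT rule would analyse 250, of whom 45 have no observed outcome.

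The choice matters because the approaches can give different estimates and intervals for one of the two outcomes that decide the trial. Freezing people at baseline pulls each arm's mean change toward zero. Age is an input to the index and follow-up runs to 36 months. A person whose other risk factors stay the same would therefore be expected to score higher at the end than at the start, and recording no change is mildly favourable to each dropout. If one arm loses more people, that credit is shared unequally.

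**Working it through.** **Inputs from the article.** 250 recruited, 125 per arm (the 102 per arm retained implies 1:1); attrition 18%; target difference 0.5 SD, equated with 13 points, so the SD is 13 / 0.5 = 26 points; two-sided alpha 0.01; planned power 80%.

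**Assumptions.** The 0.5 SD is on the scale of the change score (SD of change 1). Dropouts would have changed like those observed. Control mean change is 0 in step 2.

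**1. The plan's own figure.** 250 × 0.82 = 205, as stated. With 102 per arm, power = Φ(0.5 / √(2/102) − 2.576) = 84.0% (83.3% by the noncentral t). The difference detectable with 80% power is 0.479 SD. The plan's 80% for a difference of the order of 0.5 SD is therefore met.

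**2. Dropouts frozen at baseline.** Let q be retention and m the true mean change in an arm. The frozen data have mean qm and variance q + q(1 − q)m².

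- Effect: 0.82 × 0.50 = 0.41 SD; 0.82 × 13 = 10.7 points. At 10% dropout it is 0.45 SD; at 33%, 0.335 SD.
- Variances: control 0.82; active 0.82 + 0.82 × 0.18 × 0.25 = 0.857.
- SE: √((0.82 + 0.857)/125) = 0.116.
- SE from observed cases only: √(2/102.5) = 0.140. SE had all 250 been observed: √(2/125) = 0.126.

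**3. Coverage of the true 0.50 SD.** The estimate is displaced by 0.09 / 0.116 = 0.78 standard errors.

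- 95% interval: Φ(1.96 − 0.78) − Φ(−1.96 − 0.78) ≈ 88%.
- 99% interval: Φ(2.576 − 0.78) − Φ(−2.576 − 0.78) ≈ 96%.

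If the 0.5 SD refers instead to the outcome, analysed with baseline as a covariate, simulated 95% coverage is 86%, 82% and 59% at baseline correlations of 0.5, 0.7 and 0.9. Observed cases give about 95%.

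**4. Power.** Frozen: Φ(0.41 / 0.116 − 2.576) ≈ 83%. Observed cases: Φ(0.50 / 0.140 − 2.576) ≈ 84%. Effect and SE shrink together.

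**5. Unequal dropout, no treatment effect.** If both arms shift by g, the spurious difference is g × (difference in dropout). The article gives neither dropout by arm nor drift, so all inputs here are assumptions. With 30% lost in the active arm and 10% in control:

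| Upward drift | Points (× 26) | False benefit (SD) | Type I error (nominal 1%) |
|---|---|---|---|
| 0.10 SD | 2.6 | 0.02 | 1.1% |
| 0.20 SD | 5.2 | 0.04 | 1.5% |
| 0.30 SD | 7.8 | 0.06 | 2.1% |

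With equal dropout the spurious difference is zero and type I error stays at 1%. The sign reverses if control loses more, or if both arms improve: with 0.5 SD improvement in both and 25% v 11% lost, the bias is 0.5 × 0.14 = 0.07 SD against the active arm, with type I error about 2.5%.

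The covariate-adjusted simulation at 26% v 10% and 0.2 SD upward drift gives 1.7% to 2.5%, depending on the correlation. At 0.5 SD drift (13 points) it gives 3.9% to 13.1%.

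**The case against.** The wording is hedged: mixed models are to be used predominantly, the two analyses typically apply, and the dropout rule contains an and/or. One can read the passage as a mixed model bracketed by two supporting analyses, with the ranking left to a statistical analysis plan that is not shown. That softens the clash. It does not remove it, because the text that is shown attaches the ITT label to the imputed version.

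Three stronger readings are tempting, and the documents do not support them.

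- *The standard error is wrong.* It is not wrong for what it estimates. In simulation at 18% dropout the model SE (0.116) matches the empirical spread (0.117), and the 95% interval covers 0.41 SD in 94.8% of runs. The coverage loss in step 3 is for the undiluted effect. It comes from the displaced estimate together with an SE smaller than the observed information on that effect supports.
- *The estimate is biased whatever happens to dropouts.* This holds only if they would have changed like those observed. If they revert to baseline, 0.41 SD is correct.
- *Age in the index makes the rule anti-conservative and inflates type I error.* This needs both unequal dropout and an appreciable drift. Doubling the nominal 1% at 30% v 10% takes about 7.8 points of drift within 36 months, for which the article offers no basis.

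Nor can unequal dropout be inferred from visit burden alone. The active arm has mostly hour-long sessions against short calls. But 84% completed all sessions in the pilot, cash and vouchers are paid only in the face-to-face arm, control participants also attend one 90-minute and two 30-minute sessions, and outcome assessments are common to both arms. The objection stands on all these points.

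**Conclusion.** The concern holds in a limited form, and the wording should be fixed. The article gives incompatible missing-data rules for one primary outcome and does not say which decides it. Followed as written at 18% dropout per arm, and provided data are missing at random, the ITT rule understates the CVD effect by 18% (0.50 to 0.41 SD). Its interval covers the true effect less often than its nominal level. The cost is a distorted effect size and interval, not lost power. The rule is not guaranteed conservative, but any false benefit depends on differential dropout and drift that the article does not report. A reader might infer that type I error is inflated in this trial; the documents show only that it could be, and with equal dropout it is not.

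**What to change.** In Statistical Analysis, state that the primary ITT analysis of CVD risk is the likelihood-based mixed model fitted to the observed data of all randomised participants. Move the rule that gives dropouts their baseline CVD risk out of the ITT definition and label it a sensitivity analysis, preferably with age updated to the assessment date. Label the analysis of those who attended most sessions as supportive. Keep the convention of counting dropouts as smokers for abstinence; this point does not touch it.

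The cost is a few sentences, since the mixed model is already planned; no extra data, visits or participants are needed. The small downside is that the primary result then relies on missing at random, which the retained sensitivity analysis probes.

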#### Contingency reinforcement component

In the face-to-face condition, contingent reinforcement will be utilised, as it has been identified as an effective technique for facilitating smoking cessation amongst individuals with severe mental illness [10]. Expired carbon monoxide (CO) will be monitored each week, with positive reinforcement provided in the form of certificates and financial reimbursement (cash and vouchers) when participants meet predetermined criteria for success. The contingency reinforcement schedule will be based on a shaping model. Relative to an abstinent-only model, a shaping model rewards participants for successive reductions in CO readings as well as abstinence. This is in accordance with both abstinence and harm reduction approaches to substance use change. There are several components to this model. Firstly, session-by-session reimbursement is contingent upon demonstrated reductions in expired CO (explained in detail below). Secondly, participants receive a bonus once they meet the CO criterion for a given (set) number of consecutive weeks (e.g. three weeks in a row). Thirdly, an additional 'bonus' is on offer every week for participants who demonstrate abstinence (< 10 ppm expired CO). An advantage of this schedule is that it accounts for individual differences in baseline CO and rates of behaviour change. However, it is anticipated that many participants will be approaching and/or have met the abstinence criterion by the end of the weekly phase of treatment. As such, during the fortnightly and monthly sessions, reinforcement will be contingent upon abstinence only (<10 ppm expired CO). In summary, we will adopt a shaping schedule during the weekly phase of treatment whilst the fortnightly and monthly sessions will provide positive reinforcement only for abstinence.

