### Phone-based Condition (control)

In order to orient participants to possible lifestyle changes and in particular, NRT use, those in the phone-based condition will receive an individual 90 minute face-to-face session a week following baseline assessment, as described above. To control for the number of therapist contacts, brief, manualised telephone calls (around 10 minutes) will be conducted with participants in this condition, to 'check in' about smoking and NRT use. Therapists will complete the following formal assessments for each phone session: adverse symptom checklist (antipsychotic medication), nicotine withdrawal and current symptoms of psychosis and mood. Self-report measurements of cigarettes per day, exercise and dietary intake will be taken each week during the phone-based sessions. These phone-based sessions will be made at the same intervals as therapist visits for the Healthy Lifestyles intervention condition (i.e. weekly for eight weeks, fortnightly for three sessions, followed by monthly calls for six months). In place of the phone-based sessions at weeks 4 and 8, participants will attend face to face sessions of 30 minutes duration where NRT is dispensed, and where any problems with NRT or symptomatology are monitored. Biomedical measures (expired CO and weight) will also be taken at these two sessions.

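### The check attached to the completer analysis has no arm dimension, so by itself it can neither support nor rule out bias in the between-arm contrast among completers

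*Protocol article*

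**What the plan says.** The Statistical Analysis section says that primary outcomes will typically be analysed in two ways. The first is "intention to treat (with study dropouts regarded as continuing smokers and/or with unchanged CVD risk relative to baseline"). The second is "analyses performed within the sub-sample of participants who completed the majority of treatment sessions". The check follows directly: "comparisons on selected demographic and clinical characteristics will be made between this sub-sample and those who dropped out of treatment, to help detect any biases". The article ties these biases to the outcome measures. The sentence names two groups, completers and treatment dropouts. It neither splits them by arm nor says that the arms are combined.

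The section closes with a general rule: "As a partial control for the number of statistical tests, the threshold for significance will be set at p < 0.01". Under Outcome Measures, the secondary variables include "treatment retention and treatment alliance".

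The arms ask different things of participants. The active arm has sessions of about an hour, and "In the face-to-face condition, contingent reinforcement will be utilised", paid in cash and vouchers. In the control arm, "brief, manualised telephone calls (around 10 minutes) will be conducted with participants in this condition".

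**The concern.** Completing most sessions happens after randomisation, so the completer analysis gives up the protection of randomisation. Its arm contrast stays balanced on a baseline variable if both arms lose the same kind of patient at the same rate. It becomes unbalanced if the arms lose different kinds of patient, or the same kind at different rates. Either is plausible here, because burden and financial incentive differ between arms.

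A comparison of completers with dropouts answers another question: whether those who stay resemble those who leave. That bears on how far the completer result applies to all randomised participants. It does not measure comparability of the arms. At stake is how the completer result for CVD risk and smoking is read. A finding of no differences could be taken as reassurance about the arm contrast, and a finding of differences as evidence against it. Neither inference follows.

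**Working it through.** **Inputs from the protocol article.** 250 randomised; 205 retained, 102 per condition, at 18% attrition (Sample size calculation); two-sided 0.01 (Sample size calculation and Statistical Analysis).

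**The plan's own figure.** 250 × (1 − 0.18) = 205, or 102.5 per arm. It reproduces. The bias check has no figure of its own.

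**Assumptions not in the protocol.**
- The 18% is used for treatment dropout. The protocol gives it for study attrition: "attrition rates for CBT trials with this sample are, on average, 18% over a 12-month study period following treatment".
- One continuous baseline variable with SD 1 and equal arm means before dropout. Dropouts differ from completers by δ = 0.5 SD.
- Arms are pooled in the check, which is read at 0.01.

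**Formulas**, with dropout fraction d and shift δ in each arm, and normal approximation:
- Completer mean in an arm = −d·δ. The between-arm imbalance among completers is the difference of these two values.
- Pooled check: SE = √(1/dropouts + 1/completers), both arms together. Power ≈ Φ(difference/SE − 2.576).
- Arm-by-completion contrast: SE = √(sum of 1/n over the four arm-by-completion cells).

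**18% dropout in both arms** (22.5 dropouts and 102.5 completers per arm). Pooled SE = √(1/45 + 1/205) = 0.165. Contrast SE = √(2/22.5 + 2/102.5) = 0.329.

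| Selection | Imbalance among completers | Pooled check rejects | Arm-by-completion rejects |
|---|---|---|---|
| +0.5 in both arms | 0 | 0.5/0.165 = 3.04 → 68% | 1% |
| +0.5 and −0.5 | 0.09 + 0.09 = 0.18 SD | difference 0 → 1% | 1.0/0.329 = 3.04 → 68% |
| +0.5 in one arm only | 0.09 SD | 0.25/0.165 = 1.52 → 14% | 0.5/0.329 = 1.52 → 14% |

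Simulation with 5,000 runs per scenario agrees: 66–67% and 1–2% in the first row, 0.8–1.6% and 65–66% in the second, about 14–15% in the third.

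**30% dropout in both arms.** Pooled SE = √(1/75 + 1/175) = 0.138. Same direction: 0.5/0.138 = 3.62 → 85%, imbalance 0. Opposite directions: 1%, imbalance 0.30 SD.

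**Unequal dropout, 18% and 40%, same +0.5 shift.** Imbalance = 0.20 − 0.09 = 0.11 SD. The arm-by-completion contrast is 0 and rejects 1%. The pooled difference is 0.471 with SE √(1/72.5 + 1/177.5) = 0.139, so the pooled check rejects 79%. It fires here, but cannot be told apart from the balanced case in the first row of the table.

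**A different selection model.** Logistic completion (slope ±1 per SD), covariate–outcome correlation 0.6, no treatment effect, 3,000 runs, 82% completion:

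| Selection | Bias of completer contrast on the outcome | Pooled check rejects |
|---|---|---|
| Same in both arms | 0 | 99.8% |
| Opposite | 0.19 SD | 2.5% |
| One arm only | 0.09 SD | 53% |
| Same direction, slopes 1.5 and 0.5 | 0.07 SD | 99.3% |

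At 60% completion, opposite selection gives a bias of 0.40 SD and the check rejects 0.4%. With 60% and 82% completion and the same slope, the bias is 0.10 SD; the pooled check rejects 100% and the arm-by-completion test 1.0%.

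**From imbalance to outcome bias (first model).** Multiply by the covariate–outcome correlation: 0.18 × 0.3 = 0.05 SD, or 0.18 × 0.6 = 0.11 SD. Both correlations are assumed.

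**The case against.** The strongest reply is that the article does not say the arms are pooled. A split by arm is the kind of detail an article may leave to the analysis plan. That is fair as far as it goes, and the rejection rates above depend on pooling. What remains is that the article states a particular comparison and a purpose for it, and that comparison, as worded, does not serve the completer arm contrast.

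A reader might infer that the check stays silent whenever the contrast is biased. The calculations do not support this. Near-silence requires selection in opposite directions that cancels, and nothing in the article says selection will take that form. With unequal strength or unequal rates the check often fires. With selection in one arm only, its power is about the same as that of the arm-by-completion contrast.

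A reader might also call the 68% a false-alarm rate. It is not: completers and dropouts truly differ in that scenario, so rejection is correct for the question asked. That question has value of its own, since the article speaks of any biases and not only of bias in the arm contrast. The error would lie in carrying the answer over to the arm contrast.

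Three further points stand. The 0.18 SD is an imbalance in a covariate and should not be set directly against the 0.5 SD target effect. The 0.01 threshold is stated in general terms, so its use in this check is a reading. The check is not the only protection: the completer analysis sits beside intention to treat, potential confounders are to be modelled, and retention is a secondary outcome. Retention rates, however, do not show who was lost from each arm.

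**Conclusion.** The concern holds in limited form. As worded, the check can show that completers are unrepresentative of those randomised. By itself it can neither support nor rule out bias in the between-arm contrast among completers. It is nearly blind (about 1% rejection) to opposing selection, which at a 0.5 SD shift leaves an imbalance of 0.18 SD at 18% dropout and 0.30 SD at 30%. When it rejects, it does not show whether arm is involved.

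These sizes rest on the assumed shift, pooled arms, the 0.01 threshold, and study attrition standing in for treatment dropout. The direction of the argument does not depend on them. The intention-to-treat analysis is not directly affected. Its handling of missing outcomes concerns study dropouts, a different group from treatment dropouts, so this check does not inform that question either. This is a cheap improvement to a supporting analysis, not a fault in the main comparison.

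**What to change.** Keep the comparison of completers with dropouts, and present it by treatment arm. Add:

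- completion rates by arm;
- between-arm standardised differences in baseline characteristics among completers, with 95% confidence intervals, as the main measure of selective loss;
- optionally, an arm-by-completion contrast. It is not sufficient alone, because it misses unequal dropout rates (0.11 SD imbalance, 1% rejection above);
- the same tables for participants with and without the outcome assessment;
- a statement that a non-significant difference will not be read as absence of bias;
- a sensitivity version of the completer analysis adjusted for prognostic baseline variables.

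The cost is analysis-plan wording and a few more table columns from data already collected, with no extra participants or visits. The downside is imprecision. With 102.5 completers per arm, the 95% interval for a standardised difference is about ±1.96 × √(2/102.5) = ±0.27 SD, so the reassurance it can give is modest.
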